### Quality of life (QOL)

3.14

#### PDQ-39

3.14.1

PDQ-39 (24, 25) is a validated questionnaire specifically designed to assess quality of life in PD patients. It has demonstrated high reliability and validity and is widely applied in PD-related research. The PDQ-39 encompasses eight domains: mobility, activities of daily living (ADL), emotional well-being, stigma, social support, cognitive impairment, communication, and bodily discomfort.

#### SF-36

3.14.2

SF-36 (26) is a widely used tool for assessing health status and has been validated across multiple disease populations with strong reliability and validity. It comprises eight dimensions: physical functioning (PF), role physical (RP), bodily pain (BP), general health (GH), vitality (VT), social functioning (SF), role emotional (RE), and mental health (MH).

#### MDS-UPDRS part I

3.14.3

MDS-UPDRS represents one of the most widely used tools to assess PD progression (27). MDS-UPDRS Part I will be used in this study to assess non-motor experiences of daily living in individuals with PD. Part I consists of patient-reported items evaluating symptoms such as cognitive impairment, mood disturbances (e.g., depression, anxiety), sleep problems, pain, urinary issues, and fatigue. Higher scores indicate greater severity of non-motor symptoms. MDS-UPDRS Part I has demonstrated high internal consistency (Cronbach’s *α* = 0.85), small floor and ceiling effects (2 and 0%, respectively), and good concurrent validity (correlation with the original UPDRS Part I: r = 0.81, *p* < 0.001) (28). Its inclusion in this study will provide a comprehensive evaluation of the non-motor aspects of patient well-being, complementing the broader quality of life assessments captured by the PDQ-39 and SF-36.

### Outcomes of physical function

3.15

#### Reaction time

3.15.1

Participants will stand in a natural posture, with a signal light positioned approximately 1 meter in front of their abdomen. Upon illumination of the light, participants responded by bending their knees and jumping upward. A stopwatch will record the reaction time (s), defined as the duration between light activation and the moment the participant jumped. The test will be conducted twice, and the average score will be recorded.

#### Balance

3.15.2

##### One-legged blind balance test

3.15.2.1

The one-legged blind balance test will be used to evaluate static balance ability. Participants will stand in a natural posture, and upon hearing the “start” command, close their eyes and lift one foot. The test ended when the supporting foot moved, the lifted foot touched the ground, or the participant opened their eyes. Both the left and right foot will be tested twice, and the average duration (s) of static balance will be recorded using a stopwatch.

##### Y-balance test (YBT)

3.15.2.2

The Y-Balance Test (YBT) will be utilised to evaluate dynamic balance ability. Participants will stand at the center of a Y-shaped testing apparatus, balancing on one leg while reaching with the other leg in three directions: anterior (forward), posterolateral (backward and outward), and posteromedial (backward and inward). Participants will be required to keep their support foot stable during the test and extend the reaching leg in a controlled manner. The maximum reach distance (cm) for each direction will be recorded. Each leg will be tested twice, with the best attempt noted.

#### Physical coordination

3.15.3

##### Five times sit-to-stand test (FTSTS)

3.15.3.1

The FTSTS measured lower limb strength and coordination. Participants began in a seated position on an armless chair, backs against the upright backrest, arms crossed over the chest. Upon the “start” command, participants stand up fully and sit back down five times as quickly as possible. Timing will start when their backs lift off the chair and end when their buttocks touch the seat after the fifth repetition. FTSTS has high inter-rater reliability and test–retest reliability, with intraclass correlation coefficients (ICC) of 0.99 and 0.76, respectively. The average FTSTS completion time was 20.25 ± 14.12 s (29).

##### Timed up and go (TUG)

3.15.3.2

The TUG test assessed dynamic coordination, gait stability, and fall risk. The test will require an armrest-equipped chair, a stopwatch, and a 3-meter course marked with a thick colored line. Participants will wear their usual footwear, sit with their back against the chair, and place their hands on the armrests. Upon the “start” command, participants will stand up firmly, walk 3 meters as quickly as possible, turn around after crossing the line, walk back to the chair, turn around again, and sit down. The total time (s) taken to complete the task will be recorded.

#### Flexibility

3.15.4

##### Sit-and-reach test

3.15.4.1

The Sit-and-Reach Test assessed lower body flexibility. Participants will remove their shoes, sit on a flat surface, extend their legs forward with knees straight, and place their feet slightly apart against a measurement board. With one hand placed over the other, they will gradually reach forward. The farthest fingertip reach (cm) will be recorded, with positive values indicating a reach beyond the feet and negative values indicating a reach falling short of the toes.

##### Back scratch test

3.15.4.2

The Back Scratch Test evaluated upper limb flexibility and shoulder mobility. Participants will attempt to reach one hand over the shoulder while simultaneously bringing the other hand up from behind the back, trying to touch the fingertips of the opposite hand. The distance between the middle fingers (cm) will be recorded, where 0 cm indicates fingertips just touching, negative values represent a gap between fingertips (e.g., −5 cm), and positive values indicate overlapping fingers (e.g., +3 cm). This assessment will be executed twice with each hand in an alternating sequence. The ultimate score, measured in centimetres (cm), will be computed as the average of the optimal attempts from both arms. If participants experience pain, the test will be immediately discontinued.

#### Walking capacity

3.15.5

##### Ten-meter walk test (10MWT)

3.15.5.1

The Ten-Meter Walk Test (10MWT) will be used to evaluate gait speed under both comfortable and maximum speed conditions in individuals with PD. A total distance of 10 meters will be marked on the floor, with additional markers placed at 2 meters from the starting point and 2 meters from the ending point to define a 6-meter timed middle section. Participants will be instructed to begin walking from the starting line and continue past the finish line, walking at their normal pace during the first trial and as fast as safely possible during the second trial. Timing will commence as the participant’s leading foot crosses the 2-meter mark and will stop when the leading foot crosses the 8-meter mark, thereby excluding the initial acceleration and final deceleration phases from the timed measurement. Walking speed (m/s) will be calculated by dividing the timed distance by the time taken to complete the 6-meter section. If participants report fatigue, dizziness, or discomfort, the test will be discontinued immediately.

##### Six-minute walk test (6MWT)

3.15.5.2

The Six-Minute Walk Test (6MWT) is recommended for assessing walking capacity in people with PD by the American Physical Therapy Guidelines (30). Participants will be instructed to walk along a straight, flat 30-meter indoor corridor, turning as needed, for a total of 6 min at a self-selected comfortable pace without running or jogging. Participants may slow down or stop to rest if needed, but will be encouraged to resume walking as soon as possible. Standardized verbal encouragement will be provided each minute (e.g., “You are doing well. Keep up the good work”). The total distance walked in meters within 6 min will be recorded as the test result. The 6MWT has demonstrated convergent validity with energy cost of walking (*r* = 0.655) and excellent test–retest reliability (ICC = 0.95–0.96) in individuals with PD (31, 32). If participants report excessive fatigue, dizziness, chest pain, or other discomforts during the test, it will be immediately discontinued for safety reasons.

### Data collection and management

3.16

To ensure the accuracy and reliability of data collection, all personnel responsible for data measurement and recording underwent standardized training on operational procedures. Data monitoring will be conducted by independent personnel who are not involved in the intervention of the study. This process will include reviewing all informed consent forms, verifying data integrity, and cross-checking source documents. All data will be collected at three time points (Week 1, Week 6, Week 12) to monitor short-term and long-term effects. Data will be recorded on standardised report forms and transferred to a web-based data management system (REDCap) through multiple secure entries. Any errors identified during data entry will be corrected, with the researcher providing a signature and date for verification. Participants will have the right to withdraw from the study at any time, for any reason. In cases of withdrawal, data already collected will remain in the dataset unless the participant requests removal.

### Statistical analysis

3.17

A mixed-effect model will be employed to analyze the experimental data, accounting for individual variability. The model will assess the random effect of participants while adjusting for baseline variables. Baseline characteristics will be compared between groups using appropriate statistical tests (e.g., one-way ANOVA for continuous variables, chi-square test for categorical variables) to ensure group equivalence prior to intervention. If any significant baseline differences are found, they will be adjusted for in the subsequent analyses. To account for differences in exercise intensity and total dose between groups, weekly exercise volume (MET-hours/week) will be calculated and included as a covariate in the mixed-effect model. Intergroup comparisons will be conducted without multiple comparison adjustments. The differences in intervention effects among the three groups will be calculated and expressed as effect sizes with 95% confidence intervals (CIs). For outcome analyses, mixed-effect models will be primarily employed to analyze repeated measures across time points. When analyzing between-group differences at individual time points, one-way ANOVA or Kruskal-Wallis test will be applied, depending on data distribution and normality assumptions. Pairwise post-hoc comparisons will apply Bonferroni correction. All statistical analyses will be conducted using SPSS 26.0 and R 4.0.2, with a significance level of *p* < 0.05.

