### Sample size

3.19

The sample size estimation was based on expected changes in PDQ-39 total score, assuming a minimum clinically significant difference of 5 points between groups. Using a power of 80% (1-*β* = 0.80) and a significance level of 0.05 (two-tailed), the required sample size was calculated using G*Power 3.1. Given an estimated standard deviation (SD) of 10.5 and an effect size of 0.5, the initial calculation suggested 42 participants per group. Considering a potential 15% dropout rate, the final sample size was increased to 50 participants per group, resulting in a total of 150 participants.

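### Baseline significance tests help choose the model's covariates, and the planned single-visit group comparisons cannot use the baseline score

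*Protocol article*

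**What the plan says.** All of this stands in section 3.17 (Statistical analysis) of the protocol article.

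- **Main model.** Outcomes are analysed with a mixed-effect model: "The model will assess the random effect of participants while adjusting for baseline variables". The variables are not named, and no condition is attached. Later the section says that "mixed-effect models will be primarily employed to analyze repeated measures across time points".
- **Baseline tests.** Groups are compared at baseline by ANOVA or chi-square "to ensure group equivalence prior to intervention".
- **Trigger.** "If any significant baseline differences are found, they will be adjusted for in the subsequent analyses".
- **Single visits.** For between-group differences at individual time points, "one-way ANOVA or Kruskal-Wallis test will be applied, depending on data distribution and normality assumptions". Pairwise post-hoc comparisons are Bonferroni-corrected, although the section also says that intergroup comparisons carry no multiplicity adjustment.

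Section 3.19 sizes the trial on the PDQ-39 total score, "assuming a minimum clinically significant difference of 5 points between groups", with SD 10.5 and 42 per group before dropout.

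**The concern.** Two stated rules are poorly chosen.

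First, sections 3.3 and 3.4.1 describe randomised, concealed allocation, so a baseline difference arises by chance. A significance test then answers no useful question, and a non-significant result does not demonstrate that the groups are equivalent. Using the p-value to add covariates ignores how strongly a variable predicts the outcome, which is what determines the benefit of adjusting for it. The covariate set of the main model is therefore not settled until the data are seen.

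Second, the Week 6 and Week 12 comparisons, where they are made visit by visit, use methods that take no covariate. They discard the baseline score, although section 3.13 has every outcome measured at baseline. The choice between the two tests also depends on the observed distribution, and they answer different questions: ANOVA compares means, while Kruskal-Wallis compares rank distributions and gives no estimate on the 5-point scale. A Week 12 group comparison could thus come from the mixed model or from a per-visit test, and the two could disagree.

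**Working it through.** **Inputs.** From section 3.19: difference 5 points, SD 10.5, two-sided alpha 0.05, 42 evaluable per group. From section 3.17: Bonferroni correction of pairwise comparisons. Assumed, because the protocol article gives no value: the correlation r between the baseline and follow-up score, shown at 0.5, 0.6 and 0.7.

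**Step 1: the plan's own figure.** The dropout step reproduces: 42/0.85 = 49.4, rounded up to 50. The 42 itself does not. The two-sample normal formula gives 63 per group for an effect size of 0.5 and 70 for 5/10.5. That is a separate matter; 42 is used here only as the planned evaluable number.

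**Step 2: an unadjusted contrast.** Standardised difference d = 5/10.5 = 0.476. Non-centrality = d × √(n/2) = 0.476 × √21 = 2.18. With 82 degrees of freedom the critical value is 1.989 at alpha 0.05, and 2.444 at 0.05/3 = 0.0167. Power (non-central t) is 58% and 40%.

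**Step 3: the same contrast, adjusted for baseline.** The residual SD becomes 10.5 × √(1 − r²), so d is divided by √(1 − r²).

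| r | Cut in residual variance (r²) | d | Non-centrality | Power, alpha 0.05 | Power, alpha 0.05/3 |
|---|---|---|---|---|---|
| unadjusted | none | 0.476 | 2.18 | 58% | 40% |
| 0.5 | 25% | 0.550 | 2.52 | 70% | 53% |
| 0.6 | 36% | 0.595 | 2.73 | 77% | 61% |
| 0.7 | 49% | 0.667 | 3.06 | 86% | 73% |

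**Step 4: if 10.5 is the SD of change.** Section 3.19 speaks of expected changes, so this reading is possible. With equal variances at both visits, the raw-score SD is 10.5/√(2(1 − r)) and the adjusted residual SD is 10.5 × √((1 + r)/2). At alpha 0.05 and 42 per group:

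| r | ANOVA on raw visit scores | ANOVA on change scores | Adjusted |
|---|---|---|---|
| 0.5 | 58% | 58% | 70% |
| 0.6 | 49% | 58% | 67% |
| 0.7 | 39% | 58% | 65% |

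Adjustment gains in every row. The gain is larger against raw scores and smaller against change scores as r rises.

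**Step 5: does a significance trigger recover the precision?** A simulation with three groups of 42 looked at one contrast (20,000 null and 8,000 alternative runs) and adjusted for the baseline score only when its baseline ANOVA had p < 0.05.

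| r | Power: unadjusted / triggered / always adjusted | Type I error of triggered rule |
|---|---|---|
| 0.5 | 57 / 58 / 70% | 0.045 |
| 0.7 | 59 / 60 / 85% | 0.040 |
| 0.8 | 57 / 59 / 95% | 0.039 |

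The trigger recovers almost nothing, because it fires for a given variable in only about 5% of trials. It is slightly conservative, not anti-conservative. The simulation isolates the trigger as the sole route to adjustment; it does not represent the main mixed model.

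**Step 6: how often the trigger fires at all.** With k independent baseline tests the chance of at least one significant result is 1 − 0.95^k: 23% for 5, 40% for 10, 64% for 20. The protocol article does not fix k, and overlapping quality-of-life and mobility measures are unlikely to be independent, so these are only illustrative.

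**The case against.** The strongest reply is that the main analysis already adjusts. Section 3.17 says without condition that the mixed model adjusts for baseline variables, and it makes that model primary. A reader might infer that significance tests are the only route to adjustment, or that the main analysis wastes precision. The text supports neither: the trigger adds to a model that already adjusts, and the loss computed above belongs to the per-visit tests. This part of the reply stands.

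A reader might also infer that the trigger inflates false positives. The simulation shows otherwise. Nor does the text name a formal normality pre-test, or say how missing values are handled at a single visit, so nothing here rests on either.

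On size, the reply notes that r is assumed, that a single contrast at 0.05 is not the Bonferroni-corrected procedure, and that 10.5 may be the SD of change. All three are fair, which is why the range, both alpha levels and both readings are shown.

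Finally, naming covariates is commonly left to the SAP. That is so, and their absence is not the complaint. The trigger and the per-visit methods are rules that section 3.17 states outright. Giving the mixed model primacy does not remove the overlap either, because the section explicitly directs between-group comparisons at individual time points to the other tests.

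**Conclusion.** The point holds with limited scope. Section 3.17 states a rule that makes the mixed model's covariate set partly data-dependent and justifies it by an equivalence that baseline tests cannot establish. It also assigns per-visit comparisons to methods that cannot use the baseline score.

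For one such contrast the power forgone is about 12 to 28 percentage points at alpha 0.05 (58% against 70% to 86%), or 13 to 33 points with Bonferroni correction (40% against 53% to 73%). This assumes r between 0.5 and 0.7, 42 per arm, a 5-point difference and 10.5 as the SD of the score. If 10.5 is the SD of change, the gain at alpha 0.05 over the same range of r is 12 to 26 points against raw scores, and 7 to 12 points against change scores. No precision loss is shown for the main mixed model, and no type I error inflation is claimed.

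**What to change.** In section 3.17:

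1. Delete the baseline significance tests and the rule that adjusts for whatever proves significant. Present baseline data descriptively by group.
2. State that each outcome's mixed model always includes the baseline value of that outcome.
3. Take the Week 6 and Week 12 pairwise contrasts, with 95% confidence intervals, from that model (arm, visit and arm-by-visit), in place of ANOVA and Kruskal-Wallis.

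Any further covariates, and the handling of skewed outcomes, can be left to the SAP provided they are fixed before group data are seen. The cost is a change of wording: the baseline values are already collected, and no visit, measurement or participant is added.

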### Qigong group (QG)

3.6

Participants in the Qigong group will practise Baduanjin (Eight-Section Brocade) through live-streamed video sessions under the guidance of professional instructors. Baduanjin is a traditional mind–body exercise that integrates physical movement, breath control, and psychological regulation. It consists of eight sequential movements, primarily involving upper and lower limb coordination, head–neck control, and spinal movement, all performed in synchronisation with rhythmic breathing. Each complete session will last approximately 10 to 15 min. During the first week, participants will receive systematic instruction sessions in small groups (five participants per group, with a total of ten groups) via a two-way live video conferencing platform. Certified Qigong instructors will guide participants step by step through the eight standard Baduanjin movements so that all participants can master the basic forms and key techniques. Instructors will closely monitor each participant’s postures, breathing techniques, and movement sequences, providing real-time corrections and movement modifications when needed. This real-time, two-way format will consistently be applied in all remote sessions during the intervention period to guarantee correct practice and optimize training effectiveness. From week 2 onward, participants will engage in three 40-min remote sessions per week, which included 5 min of warm-up, 30 min of core Baduanjin practice, and 5 min of cool-down exercises under professional supervision. Participants will also be encouraged to practice independently outside of the scheduled sessions to enhance training effectiveness. Participants who withdrew from the study will be asked to provide their reasons for discontinuation.

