### Conventional exercise rehabilitation group (EG)

3.7

Participants in the conventional exercise rehabilitation group will undergo a combined aerobic and resistance training intervention, following a structured moderate period high-intensity resistance training (MP-HI-RT) + moderate period low-intensity aerobic exercise (MP-LI-AE) (23). Participants will engage in three 40-min sessions per week, guided by professional two-way live video tutorials. Each session consisted of 5 min of warm-up, 30 min of core resistance training with resistance bands, and 5 min of cool-down exercises. The resistance load will be determined based on baseline muscle strength assessments to ensure appropriate intensity for each participant. Additionally, participants will be encouraged to engage in self-paced walking exercises outside of the supervised sessions, with walking intensity adjusted according to their pre-measured aerobic capacity. Participants who withdrew from the study will be asked to provide their reasons for discontinuation.

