### Control group (CG)

3.8

Participants in the control group will not receive specific exercise guidance and will be instructed to maintain their usual daily activities. Researchers will conduct regular monthly follow-ups to assess participants’ status and to confirm that they do not engage in additional exercise interventions during the study period.

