### Adherence monitoring

3.10

To ensure participant compliance and maximize the effectiveness of the interventions, all participants in the Qigong group and the conventional exercise rehabilitation group will be required to submit weekly practice logs reporting their training completion, experience, and any discomfort. Participants may submit these practice logs in written form via email, text message, or instant messaging apps, depending on their preference and convenience. Alternatively, participants who find it difficult to submit written logs will have the option to report verbally through a scheduled phone call with a designated member of the research team. For each participant, a designated research member will maintain regular contact. If a participant does not submit their weekly report on time, the research team will proactively follow up by phone or instant messaging apps to remind them to submit their practice log. To further promote accountability and adherence, each participant will receive a minimum of two phone check-ins per month.

During these calls, the research team will:

Review the participant’s training progress and address any questions about the intervention.Provide coaching tips or practical advice to help overcome any difficulties in following the exercise program.Discuss potential barriers to adherence (e.g., time constraints, technical issues) and offer feasible solutions.Encourage participants to continue practicing regularly and highlight the importance of consistent participation for achieving the expected benefits.

These follow-up communications will be documented in the study records. If a participant repeatedly fails to submit practice logs or shows signs of poor adherence, the research team will provide additional personalized guidance and, if necessary, involve family members to support the participant’s continued engagement.

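### Weekly exercise volume, a consequence of the assigned arm and of adherence, is a covariate in the main mixed model, so the contrasts with control no longer estimate the randomised effect

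*Protocol article*

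**What the plan says.** Section 3.17 (Statistical analysis) states that "weekly exercise volume (MET-hours/week) will be calculated and included as a covariate in the mixed-effect model". The reason given is that the arms differ in exercise intensity and total dose. The same section makes this the main analysis: "For outcome analyses, mixed-effect models will be primarily employed to analyze repeated measures across time points". Baseline adjustment is a separate item: "The model will assess the random effect of participants while adjusting for baseline variables".

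The arms differ in exercise by design. In QG (3.6), from week 2, "participants will engage in three 40-min remote sessions per week". In EG (3.7), "Participants will engage in three 40-min sessions per week, guided by professional two-way live video tutorials". Section 3.3 encourages further self-guided sessions in both. In control (3.8), "Participants in the control group will not receive specific exercise guidance and will be instructed to maintain their usual daily activities", with monthly follow-up to confirm that no extra exercise is taken up.

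On measurement, Adherence monitoring (3.10) says that "all participants in the Qigong group and the conventional exercise rehabilitation group will be required to submit weekly practice logs". It sets no such requirement for CG.

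The Objectives (section 2) ask whether remote Baduanjin improves quality of life and physical function, and how it compares with conventional exercise.

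**The concern.** A covariate in a randomised comparison should be fixed before randomisation. Weekly exercise volume is not: it results from the allocation and from how well each patient adheres. Conditioning on it asks how QG and CG patients would differ if they exercised equally, which is not what the Objectives ask.

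Three things follow for QG-CG and EG-CG:

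- **Lost effect.** The part of the benefit that runs through exercise volume is credited to the covariate instead of the arm.
- **Lost precision.** Volume is correlated with arm, so the standard error of the arm contrast rises even if no effect runs through volume.
- **New bias.** Fitter or more motivated patients may both exercise more and score better. Conditioning on volume then opens a path that randomisation had closed.

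In addition, the article describes no weekly volume source for CG on the same basis as the logs in the other two arms.

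**Working it through.** **Inputs from the article (3.19, Sample size).** Difference 5 points on PDQ-39, SD 10.5, 42 evaluable per arm.

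**Assumed inputs.** The article gives no MET figures, so two sets of volumes (MET-hours/week) are used:
- Set A: CG 0.5, QG 6, EG 8; within-arm SDs 0.5, 2, 2.
- Set B: CG 4, QG 10, EG 12; within-arm SD 3 or 4 in every arm.

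A linear model at one time point stands in for the mixed model.

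**Step 1: without the covariate.** SE = 10.5 x sqrt(2/42) = 2.29. Then 5/2.29 = 2.18, which gives power of about 0.58. (This is below the 80% stated in 3.19. That is a separate matter, and nothing here depends on it.)

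**Step 2: the estimate with the covariate.** Let p be the share of the QG-CG effect carried by volume, and D the QG-CG difference in mean volume. The effect per MET-hour is 5p/D, so the adjusted contrast is 5 - (5p/D) x D = 5(1 - p):
- p = 0%: 5 points
- p = 50%: 2.5 points
- p = 100%: 0 points

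Simulation under both sets agrees. The rejection rate is about 0.09 to 0.15 at 50% and about 0.05 at 100%.

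**Step 3: the precision with the covariate.** Variance ratio = 1 + (D²/SSW)/(2/42), where SSW = 41 x the sum of the within-arm variances.
- Set A: D = 5.5, SSW = 41 x 8.25 = 338.25. Ratio 2.88; SE = 2.29 x 1.70 = 3.9.
- Set B, SD 3: D = 6, SSW = 41 x 27 = 1107. Ratio 1.68; SE = 2.29 x 1.30 = 3.0.
- Set B, SD 4: D = 6, SSW = 41 x 48 = 1968. Ratio 1.38; SE = 2.29 x 1.18 = 2.7.

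At p = 0% the estimate is unbiased, but power is 0.24 (Set A) to about 0.45 (Set B, SD 4).

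**Step 4: confounding when there is no true effect.** Suppose an unmeasured factor loads L on both volume and outcome. The pooled within-arm slope is L² x 10.5 x (sum of SDs)/(sum of variances), and the bias in QG-CG is that slope x D.
- Set A, L = 0.5: 0.25 x 10.5 x 4.5/8.25 = 1.43; x 5.5 = 7.9 points.
- Set B, SD 3, L = 0.5: 0.25 x 10.5/3 = 0.875; x 6 = 5.2 points.
- Set A, L = 0.3: 0.09 x 10.5 x 4.5/8.25 = 0.515; x 5.5 = 2.8 points.
- Set B, SD 4, L = 0.3: 0.09 x 10.5/4 = 0.236; x 6 = 1.4 points.

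The bias is therefore about 1.5 to 8 points in magnitude, with simulated false-positive rates of about 9 to 56% (repeat runs move these by a point or two). Adding a baseline covariate correlated 0.7 with the factor lowers this to about 0.8 to 4.4 points and 6 to 22%.

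**Step 5: QG against EG.** Here D = 2 in both sets. The variance ratio is 1 + (4/338.25)/(2/42) = 1.25 in Set A and 1 + (4/1968)/(2/42) = 1.04 in Set B with SD 4. The harm is much smaller than for the control contrasts.

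**The case against.** **The covariate might be a baseline habit.** The text does not read that way. Its purpose is given as "To account for differences in exercise intensity and total dose between groups, weekly exercise volume (MET-hours/week) will be calculated and included as a covariate", which describes the exercise delivered, and baseline variables are listed separately.

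**The model may not remove the whole effect.** This stands. A reader might infer that adjustment wipes out the treatment effect, but that needs the whole effect to run through volume. The article states no such share, and it describes Baduanjin as also working through breathing and mental regulation, which MET-hours do not measure.

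**Control volume need not be near zero.** This also stands. CG keeps its usual activities, and the article does not say whether habitual activity counts. Set A is the harsher assumption and Set B the milder one.

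**Two inferences about CG data are unsupported.** One is that coding CG as zero would duplicate the arm indicator. It would not: volume still varies within QG and EG, the design matrix keeps full rank, and arm explains about 80% of volume under Set A. The other is that missing CG volumes would drop the control arm. The article does not say how CG volume is obtained or how missing values are handled, and it may leave both to a fuller document.

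**The largest bias figure is a worst case.** The 7.9 points leave out the planned baseline adjustment. Such adjustment reduces the bias in Step 4 but does not remove it.

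**Dose adjustment may be deliberate for QG against EG.** That is a fair secondary question, but its answer is not the randomised effect. The text does not limit the covariate to that contrast.

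**Unadjusted tests remain.** The ANOVA or Kruskal-Wallis tests at single time points are described without the covariate. They are not the main analysis, and they target a different effect from the mixed model.

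**Conclusion.** The point holds: the covariate is wrong as written for QG-CG and EG-CG in the main model. Those contrasts lose the part of the effect carried by exercise volume, lose precision, and are open to confounding that randomisation had excluded. The direction of the problem follows from the design. Its size rests on the assumed volumes, the assumed mediated share and the assumed strength of any common cause, none of which the article gives. In none of the cases examined is the adjusted control contrast both unbiased and as precise as the unadjusted one. The documents do not support the stronger claims that the effect is necessarily removed in full or that the control arm would drop out of the analysis.

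**What to change.** In section 3.17, delete MET-hours/week from the primary and secondary outcome models. Estimate the arm contrasts as randomised, adjusting only for pre-randomisation variables such as the baseline value of the outcome. Report MET-hours/week descriptively by arm, and state how it is obtained in CG. If dose is of interest, specify a dose-adjusted QG-EG comparison or a dose-response or mediation analysis separately, labelled exploratory and non-randomised.

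The core change is one sentence. It needs no new data or patients, and it should be made before any outcome analysis by arm.
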